#### **11.2.4.3 Analysis of count outcomes**

The count outcome will be summarised using the number of events (e.g. days with fever, days with respiratory symptoms, days with low O2 saturation, etc.) and incidence rate by group and will be analysed by a GLM model with the predictor as exposure variable and with Poisson distribution and log link function, and the stratification factors 'study site' as covariates. Incidence rate ratio with their two-sided 95% CIs will be derived from the GLM model.

#### **11.2.4.4 Immunological responses**

Antibody titres to COVID-19 and malaria and other pathogens will be summarised by mean fluorescence index (MFI) and geometric mean titre (GMT) (95% CI) by group at different time points. The analysis will consider:  $C_{max}$ , maximum antibody signal allowing for  $\Delta_c$  the maximum change in antibody signal (i.e. including baseline measure);  $t_{max}$ , time to maximum antibody signal which equates to seroconversion;  $t_{1/2}$ , the half-life of antibody signal (in days) after a maximum signal has been reached; and  $t_{neg}$ , modelled time until the signal is reduced to below the level of detection of the assay.

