| Secondary objectives                                                                                                                                                                                                                                                                 | Secondary endpoints                                                                                                                                                                                                                                                                                                                                                                                                    |
| 
 
To determine if pyronaridine-artesunate compared to artemether-lumefantrine alters the viral load and/or the duration of SARS-CoV-2 viral shedding
 
                                                                                 | 
 
Median viral load of SARS-CoV-2 detected from mid-nasal swabs by PCR
 
Cumulative incidence of SARS-CoV-2 clearance (defined as the proportion of participants with negative nasal swabs) by days 14, 21 and 28
 
Time to clearance of nasal SARS-CoV-2, defined as negative SARS-CoV-2 RNA PCR tests (swabs collected on days 1, 3, 7, 14, 21 and 28)
 
 |
| 
 
To determine if treatment of malaria infection with pyronaridine-artesunate in COVID-19 patients alters the antibody response to SARS-CoV-2 infection compared to treatment with artemether-lumefantrine
 
                           | 
 
Cumulative seroconversion rates (IgG, IgM, IgA) by days 7, 14, 21 and 28, and IgG, IgM, IgA antibody titres against SARS-CoV-2 by day-28 expressed as the geometric mean, maximum, and change from baseline
 
                                                                                                                                                          |

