| 
 
To test the safety of pyronaridine-artesunate compared to artemether-lumefantrine in COVID-19 patient coinfecting with malaria parasites
 
                                                                                           | 
 
The cumulative proportion of treatment-related adverse events and serious adverse events and adverse events resulting in treatment discontinuation by day 7
 
                                                                                                                                                                                                          |
| 
* The cumulative seroconversion rate is defined as the proportion of participants with a positive antibody test per period among those with a negative antibody test on enrolment.
                                                                                            |                                                                                                                                                                                                                                                                                                                                                                                                                        |

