### 5.1.3 Nested malaria treatment trial within the COVID-19 cohort study (N~142)

In addition, we will conduct a nested exploratory, 6-week, open-label, 2-arm, randomised controlled nested malaria treatment trial in the COVID-19 patients co-infected with malaria with mild disease who are able to take oral medication. We will compare pyronaridine-artesunate and artemether-lumefantrine to assess whether, in COVID-19 patients with malaria, treatment with quinoline antimalarials (pyronaridine) affects the seroconversion rate or time to seroconversion to SARS-CoV-2 or reduce viral load and duration of shedding relative compared to patients receiving AL. The patients enrolled in this nested malaria treatment trial will have an additional follow-up visit at days 21 and 42.

The follow-up schedule in the treatment study will be identical to that in COVID-19 patients without malaria to allow for comparison between disease progression between COVID-19 with and without malaria.

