#### **9.2.5 Close-out visit day 42 nested malaria treatment trial**

In additional malaria-specific close-out visit will take place on day 42 in the patients enrolled in the nested malaria treatment trial to assess the therapeutic response to the antimalarials. The rationale for this additional day-42 visit is based on the standard 6-week duration of follow-up recommended by WHO for treatment efficacy studies of antimalarials.

### 9.2.6 Extended follow-up visits at month 3, 6, and 12

Funding permitting, participants will be asked to return to the clinic for extended follow-up visits 3, 6, and 12 months after enrolment to assess the longevity of the antibody responses to SARS-CoV-2. A sample for malaria RDT, microscopy and PCR will be taken to continue to determine any associations between malaria co-infection and persistence of SARS-CoV-2 immune responses.

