### 10.4.2 Antibody Testing

Serum samples for serology collected at days 0, 1, 3, 7, 14 and 28, 42, and at 3, 6, and 12 months will be tested for IgA, IgM, and IgG antibodies to SARS-CoV-2 and malaria-specific antigens and other infections. Avidity of SARS-CoV-2 antibodies will also be measured, and a sub-set of serum samples will be used for neutralising assays in order to relate antibody levels to viral neutralising activity.

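### Section 11.2.4.4 equates time to peak antibody signal with seroconversion, which contradicts the positive-test definition in section 4

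*Protocol*

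**What the plan says.** Section 11.2.4.4 names the antibody parameters to be considered: the maximum signal, the maximum change, t_max, the half-life after the maximum, and the modelled time until the signal falls below detection. It describes t_max as "time to maximum antibody signal which equates to seroconversion".

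The footnote to section 4.3 defines the cumulative seroconversion rate as "the proportion of participants with a positive antibody test per period among those with a negative antibody test on enrolment". The nested-trial endpoint is "Cumulative seroconversion rates (IgG, IgM, IgA) by days 7, 14, 21 and 28". The same row lists titre separately: "IgG, IgM, IgA antibody titres against SARS-CoV-2 by day-28 expressed as the geometric mean, maximum, and change from baseline". The maximum is therefore already a different quantity from seroconversion.

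Timing is a stated interest. Section 5.1.3 says the nested trial will assess whether pyronaridine "affects the seroconversion rate or time to seroconversion to SARS-CoV-2". Section 3.2.2 raises time to seroconversion for the malaria comparison, and section 7.4 names it among the objective assessments.

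Section 10.4.2 gives the sampling: "Serum samples for serology collected at days 0, 1, 3, 7, 14 and 28, 42, and at 3, 6, and 12 months". Section 9.2.6 makes the later visits conditional: "Funding permitting, participants will be asked to return to the clinic for extended follow-up visits 3, 6, and 12 months after enrolment". Sections 5.1.2, 5.1.3 and 9.2.2 give days 21 and 42 to nested-trial participants only.

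**The concern.** The section 4 footnote defines the rate of seroconversion but not its timing. Section 11.2.4.4 is the only place where the protocol attaches a time to the event, and it attaches the time of the peak. An analyst following that sentence would report when the response was highest as when the participant became positive.

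What is at stake is the time-to-seroconversion result, both for pyronaridine-artesunate against artemether-lumefantrine and for malaria-positive against malaria-negative participants. It could also disagree with the cumulative seroconversion rates in the same report, because the two would rest on different events.

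**Working it through.** **1. The plan's own figure.** The only planning figure for seroconversion is in section 11.1.3: 80% power for 50% against 25% or 75% by day 14, with 142 randomised and 10% loss.
- Completers: 142 × 0.9 = 127.8, rounded to 128, or 64 per arm.
- Fisher's exact test, two-sided 0.05, 64 per arm: power 80.2% in either direction. The stated 80% is reproduced. A pooled z-test gives 84.0%.
- The calculation compares proportions seroconverted by day 14. It does not use t_max, so the wording in 11.2.4.4 leaves it unchanged.

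**2. The two definitions compared.**
- *Event.* Section 4: a positive test. Section 11.2.4.4: the highest signal in the series.
- *Who has one.* Section 4: only people negative at enrolment, and only if they turn positive. Section 11.2.4.4: any measured series has a maximum, and no restriction is stated. The cohort criteria in 6.2.2 do not exclude people already antibody-positive.
- *Order.* For one antibody class in one participant, the highest sample is at least as high as any positive sample. It is therefore itself positive and cannot precede the first positive. So t_max is at or after the first positive, never before it.

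**3. How far apart they are.** The documents give no antibody kinetics, so the following are assumptions. Simulations used 20,000 participants per scenario. Peak day was uniform over the stated range. The log signal rose by 1.5 per 7 days before the peak and then declined with the stated half-life. Noise had SD 0.2 on the log scale, and positivity was set at 10% of peak. Sampling was on days 1, 3, 7, 14 and 28 (cohort) or days 1, 3, 7, 14, 21, 28 and 42 (nested trial), each with or without days 90, 180 and 365.

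Each cell gives the share with t_max at the last sample, then median t_max (day), then median first positive (day).

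| Peak; half-life | Cohort to day 28 | Nested to day 42 | Cohort to month 12 | Nested to month 12 |
|---|---|---|---|---|
| day 7–21; 20 d | 38%; 14; 7 | 0%; 21; 7 | 0%; 14; 7 | 0%; 21; 7 |
| day 14–35; 60 d | 96%; 28; 14 | 41%; 28; 14 | 0%; 28; 14 | 0%; 28; 14 |
| day 14–35; 180 d | 97%; 28; 14 | 51%; 42; 14 | 0%; 28; 14 | 0%; 42; 14 |
| day 28–60; 90 d | 100%; 28; 28 | 97%; 42; 42 | 0%; 90; 90 | 0%; 90; 42 |

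- Early peaks: median t_max trails the median first positive by 14 − 7 = 7 to 21 − 7 = 14 days.
- Intermediate peaks: by 28 − 14 = 14 to 42 − 14 = 28 days.
- Late peaks: the medians coincide on three of the four schedules.

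**4. Dependence on visits.** Within a row the kinetics are identical, so any difference between the cohort and nested columns comes from the visit days. To month 12, median t_max differs by 21 − 14 = 7 days in the first row, 0 in the second, 42 − 28 = 14 in the third and 0 in the fourth. This touches the malaria comparison. The two treatment arms share one schedule.

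In the last row the observed first-positive day also differs by schedule (90 against 42). First positives therefore need to be treated as intervals between visits, not as exact dates.

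**The case against.** The strongest reply is that this is one loose clause in a list of descriptive parameters. The listed seroconversion endpoint is the cumulative rate, and time to seroconversion appears in the rationale and design text but not in the endpoint tables. Nothing says that 11.2.4.4 overrides the footnote's restriction to people negative at enrolment. The nested trial is exploratory, and detailed methods are left to the SAP. Most of this stands, and it limits the point to a secondary or exploratory one.

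It does not remove the point. Carrying the footnote's restriction into 11.2.4.4 would settle who is counted, but the recorded time would still be that of the peak. Nor is this a detail left open for the SAP: the protocol states an equivalence, and it is wrong.

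A reader might infer three stronger things, none of which the documents support.
- *That t_max falls on the last sample for nearly everyone.* Serology continues to day 42 and months 3, 6 and 12. Section 11.2.4.4 plans a half-life after the peak, and section 4.2 plans seroreversion rates. Shares near 100% need a cut at day 28 or 42 with sufficiently late peaks, or a curve that never declines. The protocol states no such cut.
- *That a true delay would be lost.* The cumulative rates by days 7, 14, 21 and 28 would still show it.
- *That the direction of an effect would reverse.* This has not been shown.

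**Conclusion.** Wrong as written, with secondary or exploratory impact only. The contradiction between 11.2.4.4 and the section 4 footnote rests on the text alone, as does the ordering argument.

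The size depends on kinetics and an analysis window that the protocol does not give. Under the assumptions above, median t_max is 7 to 28 days after the median first positive for early or intermediate peaks, and mostly equal to it for late ones. The share with t_max at the last sample is about 0% with follow-up to month 12, 38% to 100% if cut at day 28, and 0% to 97% if cut at day 42. Because months 3 to 12 depend on funding, which of these applies is not settled.

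No primary endpoint, sample size or listed cumulative seroconversion endpoint changes.

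**What to change.** In section 11.2.4.4:
- Delete the clause that equates t_max with seroconversion.
- Report t_max only as time to peak signal, state its window, and use the same visits in the groups being compared. For malaria-positive against malaria-negative participants, that means leaving out days 21 and 42.
- Take time to seroconversion as the time to the first positive test among participants antibody-negative at enrolment, by antibody class, allowing for interval censoring between the last negative and first positive visit. The model can be left to the SAP.

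The cost is a sentence or two of protocol text. The assay data are the same and no new samples are needed.

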### **11.2.5 Additional statistical consideration for the nested malaria treatment trial**

#### **11.2.5.1 Baseline characteristics**

The number of participants, their baseline demographics and characteristics, including age, height, weight, sex, race, and country etc., will be summarized by treatment group using descriptive statistics (mean, standard deviation, median, minimum and maximum for continuous and rates for categorical).

#### **11.2.5.2 Assessment of efficacy**

Similar approaches as for the COVID-19 cohort study will be used to assess treatment efficacy for binary, count and continuous data, using treatment arm as the main exposure variable of interest, and the stratification factors study site and presence of symptoms as co-variates in the crude analysis. Secondary analyses include covariate-adjusted analysis to determine whether the estimate of treatment-effect is affected with the inclusion of additional covariables, and per-protocol analysis, and sub-group analysis. Imputation for baseline missing covariates will be carried out before categorising. Assessment of the homogeneity of treatment effect by a subgroup variable will be conducted by a GLM with the treatment, subgroup variable, and their interaction term as predictors, and the P-value presented for the interaction term.

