| 16
32
41
42 | Key inclusion criteria
COVID-19 cohort study
6.2.2.1, COVID-19 cohort study, Inclusion criteria
9.1.1, Pre-screening with point of contact (POC)
SARS-COV-2 antigen tests
9.2.1, Pre-Screening (Day 0/1) | Added a positive antigen lateral flow test as part of the inclusion criteria for the COVID-19 cohort study

Removed 'not previously diagnosed with Covid-19' as exclusion criteria as this history cannot be reliably assessed. Instead, the presence of SARS-COV-2 antibodies at enrolment will now be taken into account in the analysis. |
| 16
32
43       | 2.2.3, Trial registration data, key inclusion criteria
6.2.3.1, Inclusion criteria
9.2.1.3Nested malaria treatment trial                                                                                          | Updated the inclusion criteria for the nested malaria treatment study to include the HRP2 band on the malaria RDT
"Confirmed malaria infection by RDT ( HRP2 or pLDH ) or microscopy"                                                                                                                                                   |
| 19
63             | 2.2.4, Schedule of activities;
12.7.1.4, Maximum blood volume;
Figure 5                                                                                                                                           | The required blood volume in adults and older children above the age of assent was changed from 5 to 15 mL at the 3, 6, and 12 month follow-up visit                                                                                                                                                                                              |

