#### 11.1.2 Immunological components

Serological assays will involve all cohort participants. Detailed immunological assays such as the chemo/cytokine panel and T and B cell response will be conducted from the stored samples of approximately 45 malaria cases and a similar number of matched malaria negatives per country, i.e., approximately 90 per country or 180 overall. The sample size may increase if more funding becomes available.

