## 11.2.4 Analytical methods by type of endpoint measure

### 11.2.4.1 Binary endpoints

For single measurements of binary endpoints, including for the binary primary endpoints of the screening study (cross-sectional survey, source population), COVID-19 cohort study and the nested malaria treatment trial, a generalised linear model (GLM) with the log-link function and binomial distribution (log-binomial regression) will be used to compare endpoints between exposure groups (e.g. by malaria status at enrolment). Crude GLM models will have the predictor of interest (e.g. malaria status at enrolment) as the only predictor and 'study site' as covariates. Results will be expressed as the risk ratio (RR) with associated 95% CI. If the log-binomial regression models do not converge, the 'binreg' or 'difficult' options (in that order) will be specified in Stata. If all models fail to converge, log-Poisson regression with a sandwich variance estimator will be used. Because the effect of malaria on COVID-19 may be biased by predictors that are not equally distributed by other predictors of COVID-19 severity, such as age, we will also conduct adjusted analyses to determine whether the effect of malaria on COVID-19 is affected with the inclusion of additional covariables. For repeated measurements of binary endpoints, a generalised linear mixed model (GLMMIX) with the log-link function and binomial distribution (log-binomial regression) will be used.

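### Enrolment SARS-CoV-2 serostatus is measured in the whole cohort, but section 11.2 names no severity or clearance model that uses it; it should be pre-specified for Day-7 clearance and named in the adjusted cohort analysis

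*Protocol*

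**What the plan says.** **Eligibility.** The cohort criteria (Protocol 6.2.2.1 and 6.2.2.2) contain no exclusion for earlier COVID-19. The version 2.0 change table gives the reason: "Removed 'not previously diagnosed with Covid-19' as exclusion criteria as this history cannot be reliably assessed". It continues: "Instead, the presence of SARS-COV-2 antibodies at enrolment will now be taken into account in the analysis". It does not say which analysis, or how.

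**Measurement.** Section 11.1.2: "Serological assays will involve all cohort participants". Section 10.4.2 gives the timing: "Serum samples for serology collected at days 0, 1, 3, 7, 14 and 28, 42, and at 3, 6, and 12 months". A baseline value is therefore planned for all of the roughly 708 cohort members.

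**Models.** For binary endpoints, including the cohort primary, section 11.2.4.1 states: "Crude GLM models will have the predictor of interest (e.g. malaria status at enrolment) as the only predictor", with study site as covariate. Adjusted analyses follow, with age as the only example of a covariate. For the nested trial, section 11.2.5.2 has treatment arm plus "the stratification factors study site and presence of symptoms as co-variates in the crude analysis". Covariate-adjusted analyses are secondary and their covariates are not named. Section 11.2.1 leaves detail to the SAP.

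**Explicit uses of baseline antibody.** The footnote in section 4.3 restricts seroconversion to participants who are antibody-negative at enrolment. Section 11.2.4.4 uses the baseline measure in the maximum change in antibody signal. Neither concerns severity or viral clearance.

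**The concern.** Prior immunity plausibly predicts both primary outcomes: progression by day 28 in the cohort and a negative swab on Day 7 in the nested trial. The two comparisons are affected differently.

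- **Nested trial.** Allocation is random, so what is at stake is precision. The trial expects only 134 completers and is sized at 80% power for a large effect.
- **Cohort.** Malaria status is not randomised. If earlier infection is more or less common among malaria-positive patients, part of the malaria risk ratio could reflect prior immunity. Section 11.2.4.1 itself warns about unequally distributed predictors, and section 11.1.1 allows a 35.6% sample-size inflation for adjustment, but this factor is not named.

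A covariate left open can be included or omitted once results are known. That matters more for a variable described as the replacement for an eligibility criterion.

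**Working it through.** **1. The plan's own figures (two-sided 0.05, pooled variance, no continuity correction).**
- Nested trial, section 11.1.3: 67 per arm, 20% v 42.2% gives power 0.7996; 80% is stated.
- Cohort, section 11.1.1: 135 v 538 completers, 45% v 30% gives power 0.903; 90% is stated.

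Both reproduce, and this point contests neither.

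**2. Nested trial: gain from serostatus.** The documents give no seroprevalence and no effect of prior immunity, so these are assumptions: 25% seropositive, and clearance on artemether-lumefantrine averaging 20%, for example 0.25 × 40% + 0.75 × 13.3% = 20%. Overall clearance on pyronaridine-artesunate is held at 42.2%. I simulated an unadjusted score test against a Cochran–Mantel–Haenszel test stratified by serostatus. The range in each row covers the scale (risk ratio, odds ratio or risk difference) on which the effect is held constant.

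| Control clearance, seropositive / seronegative | Unadjusted | Stratified |
|---|---|---|
| 30% / 17% | about 80–81% | 81–82% |
| 40% / 13% | about 80–81% | 83–86% |
| 50% / 10% | about 80–81% | 86–88% (odds ratio or risk difference only) |

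The last row cannot use a constant risk ratio of 2.11, because 50% × 2.11 = 105.5%. A wider grid (10–50% seropositive, constant risk ratio) gives stratified power of 80–81% if seropositives clear 1 to 1.5 times as often as seronegatives, 81–83% at 2 times, and 85–86% at 3 times. Type I error stays near 5% in both tests. Site and symptoms were left out of both tests.

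**3. Cohort: size of possible confounding.** Let s1 and s0 be the seropositive shares with and without malaria, and r the risk ratio of progression in seropositives v seronegatives. The malaria risk ratio is multiplied by

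[1 − s1(1 − r)] / [1 − s0(1 − r)].

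- s1 = s0: factor 1.00 whatever r is.
- s0 = 20%, s1 = 30%, r = 0.3: (1 − 0.21)/(1 − 0.14) = 0.79/0.86 = 0.92. With r = 0.7: 0.91/0.94 = 0.97.
- s0 = 30%, s1 = 50%, r = 0.3: 0.65/0.79 = 0.82.
- s0 = 40%, s1 = 20%, r = 0.3: 0.86/0.72 = 1.19.

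A true risk ratio of 1.5 would read as 1.5 × 0.82 = 1.23 at one extreme and 1.5 × 1.19 = 1.79 at the other. With 30% held in the malaria-negative group, factors of 0.95, 0.90 and 0.85 reduce the crude 90% power to about 80%, 64% and 45%. All these inputs are assumptions.

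**The case against.** The strongest reply is that the quoted models are the ones the protocol calls crude. Adjusted analyses are planned in both sections, the cohort sample size allows for adjustment, and covariate lists are commonly SAP matter. A reader might infer from section 11.2 that no severity or clearance analysis will use serostatus. The documents do not support that: the lists are open, the SAP is not at hand, and the change table states an intention to use it. A change-table entry that is not echoed in section 11 is also not an error in itself. What stands is that the main models are stated, serostatus is in neither, and a baseline value already planned could improve one of them.

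A second reply concerns the remedy. Enrolment antibody is not a clean marker of earlier infection. Section 16.9.1 notes that antibody rises quickly after symptom onset and can indicate early infection, and it may also follow vaccination. Whether malaria alters the antibody response is a cohort objective in section 4.2, so serostatus may lie downstream of malaria. Adjusting for it, or restricting to seronegatives, could then add bias. This stands, and it argues against putting serostatus in the main cohort model. It does not touch the randomised comparison, provided the sample is taken before treatment.

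A reader might also conclude that prior vaccination goes unrecorded. That cannot be shown, because the questionnaires are a separate document (section 16.11).

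**Conclusion.** The point holds in limited form: earlier infection is admitted, enrolment antibody is planned for everyone, and section 11.2 names no severity or clearance model that uses it.

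For Day-7 clearance the consequence is forgone precision: power of 81–88% instead of about 80% under the assumed values, with almost no gain if serostatus is weakly prognostic. It would be wrong to read this as confounding of the treatment comparison, since randomisation removes that in expectation.

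For the cohort, the tempting reading is that the malaria risk ratio is confounded by prior immunity. The documents give no link between malaria and serostatus, so only possible confounding can be claimed. Its direction is unknown, the assumed bias factor runs from 0.82 to 1.19, and it vanishes if the two are unrelated. Nothing in the stated sample-size figures is wrong on this account.

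**What to change.** 1. **Nested trial (section 11.2.5.2).** Add enrolment serostatus (positive/negative, from the Day 0/1 sample taken before the first dose) to site and symptoms as a pre-specified covariate in the Day-7 clearance model.
2. **Cohort (section 11.2.4.1).** Keep malaria status plus site as the main model. Name serostatus as a covariate in the adjusted progression analysis. Report the malaria risk ratio with and without it, and in seronegatives, as supportive estimates.
3. **Interpretation.** State that enrolment antibody may reflect current infection or vaccination and may be altered by malaria, so that the adjusted cohort estimate is not read as automatically free of confounding.

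If the sponsor does not want this, section 11.2 should say how enrolment antibody will be taken into account instead.

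**Cost.** One model term and one subset estimate, from an assay already planned. At the planning rates the nested model has about 67 × 0.20 + 67 × 0.422 = 42 events, so one more term adds a little to the risk of non-convergence; section 11.2.4.1 already has a fallback for that. Missing serostatus can follow the baseline-covariate rule in section 11.2.6.1, extended to the main nested model.
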